### **3. STUDY DESIGN**

#### **3.1 Study Design**

This is a prospective, single-arm, descriptive clinical study to observed the safety and immunogenicity profile of the use of AdimFlu-S (2011-2012 season) vaccine in pregnant female subjects. All eligible participates will receive one dose of vaccine (0.5 mL) by intramuscular injection into the upper arm. Blood serum prepared from blood samples will be collected from each maternal subject immediately prior to vaccination and 4 weeks after vaccination; moreover, blood sample at the end of the gestation period (delivery) and the cord blood sample will also be collected, if applicable. Anti-hemagglutinin (HA) antibody titers will be determined using the WHO hemagglutination inhibition reference technique and the analysis will be observer-blinded. Safety outcomes included immediate reactions at the time of vaccination, solicited local and systemic reactions for 7 days, unsolicited adverse events until the first post-vaccination serum collected, and serious adverse events and adverse events of special interest until 8 weeks after the delivery.

#### **3.2 Number of Subjects**

Sixty subjects will be enrolled..

#### **3.3 Subject Selection Criteria**

##### **3.3.1. Inclusion Criteria**

Subjects meeting all of the following criteria will be considered for admission to the study:

1. Pregnant female aged  $\geq 18$  years old.
2. Subject is pregnant for at least 3 months, inclusive.

3. Subject is willing and able to adhere to visit schedules and all study requirements.
4. Subject has read and signed the study-specific informed consent.

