### **2.3 Outcome Measure**

- Number of participants with seroprotection against influenza A/H1N1, A/H3N2, B virus (Day 28, the end of gestation period).
- Number of participants with seroconversion against influenza A/H1N1, A/H3N2, B virus (Day 28, the end of gestation period).
- Geometric means of post- to pre-vaccination antibody titer ratios against influenza A/H1N1, A/H3N2, B virus (Day 28, the end of gestation period).
- Number of participants reporting solicited subjective local reactions within 7 days (Day 1-7) post vaccination.
- Number of participants reporting solicited subjective systemic reactions within 7 days (Day 1-7) post vaccination.

- Number of participants reporting maternal complications of pregnancy, labor and delivery.
- Number of participants reporting neonatal complications.
- Number of participants reporting vaccine-associated serious adverse events (SAEs) during the study.

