At the end of gestation period, blood samples from maternal subjects and from the cord blood will be collected, if applicable. Pregnancy outcome, including but not limited to the status of delivery, abortion and the date and/or the week of pregnancy of the event, will be recorded. The child information, including but not limited to the birth height and weight of the infant, sex of infant, Apgar score at 1 min and 5 min, and other information specified in the CRF, will be collected. All serious adverse events and adverse events of special interest will be followed until 8 weeks after the delivery.

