## 5.4 Schedule

The following table details the study schedule of procedures for study period:

|                              | Visit 1 |        |          | Visit 2               | Visit 3          | Follow-up              |
|------------------------------|---------|--------|----------|-----------------------|------------------|------------------------|
|                              | Week 0  | Week 1 | Week 2~3 | Week 4  | Delivery /Birth  | 8 Weeks after Delivery |
| Inform Consent               | X       |        |          |                       |                  |                        |
| Inclusion/Exclusion Criteria | X       |        |          |                       |                  |                        |
| Vital Signs                  | X       |        |          | X                     |                  |                        |
| Weight and Height            | X       |        |          |                       |                  |                        |
| Medical History              | X       |        |          |                       |                  |                        |
| Pregnancy History/Outcome    | X       |        |          |                       | X                |                        |
| Serum Samples                | X       |        |          | X                     | X  |                        |
| Dosing                       | X       |        |          |                       |                  |                        |
| Adverse Events               | X-----X |        |          |                       | X  | X        |
| Reactogenicity events        | X-----X |        |          |                       |                  |                        |
| Diary Card                   | X-----X |        |          |                       |                  |                        |
| Concomitant Medications      | X-----X |        |          |                       |                  |                        |

: The subject will return to the site for blood sampling according to her regular check-up schedule. However, the interval between the first and second blood sampling should be at least 3 weeks apart and no more than 5 weeks.

: Including maternal serum (within 8 weeks after delivery) and cord serum

: Serious adverse events and adverse events of special interest should be collected

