## **7.3 Demographics**

Descriptive statistics for demographic and subject characteristics prior to study vaccination including age, weight, height, gravidity and week of gestation will be reported.

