## **7.4 Analysis of Immunogenicity**

The immune response to the three vaccine viral strains is assessed by calculation of the geometric mean titers (GMT) of anti-HA antibodies, geometric means of post- to pre-vaccination antibody titer ratios (GMTR, with 95% confidence intervals), seroprotection rates (percentage of subjects with a titer  $>1:40$  at 4 weeks after vaccination and at the end of gestation period), seroconversion rates. The seroconversion rate is defined as the percent of subjects with a pre-vaccination titer  $< 1:10$  achieving a titer  $\geq 1:40$  or with pre-vaccination titer  $\geq 1:10$  having at least a four-fold rise at 4 weeks after vaccination and at the end of gestation period. As for the rate of seroprotection and seroconversion rate, the 95% exact (Clopper-Pearson) confidence interval will be provided as well.

European Agency for the Evaluation of Medicinal Products/Committee for Proprietary Medicinal Products (CPMP) immunogenicity criteria for licensed influenza vaccines specifies 70% seroprotection or 40% seroconversion, or a GMTR of 2.5 for individuals between 18 and 60 years of age.[12]

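### The end-of-gestation antibody results and the cord–maternal comparison are confounded with time since vaccination, because entry has no upper gestational limit and the maternal sample may be drawn up to 8 weeks after delivery

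*Protocol*

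**What the plan says.** **Entry.** Section 3.3.1 sets a floor on gestation, "Subject is pregnant for at least 3 months, inclusive". Neither the four inclusion criteria nor the twelve exclusions set a ceiling. The nearest is a general requirement, "Subject is willing and able to adhere to visit schedules and all study requirements", which a woman near term can meet.

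**Sampling.** Visit 2 is tied to vaccination: section 5.4 requires that "the interval between the first and second blood sampling should be at least 3 weeks apart and no more than 5 weeks". The third sampling is tied to delivery instead. Section 5.1 says "At the end of gestation period, blood samples from maternal subjects and from the cord blood will be collected, if applicable", with no minimum or maximum time since the dose. A footnote to the schedule in section 5.4 widens the maternal part, "Including maternal serum (within 8 weeks after delivery) and cord serum", and section 5.5 repeats that window.

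**Analysis.** Section 2.3 lists "Number of participants with seroprotection against influenza A/H1N1, A/H3N2, B virus (Day 28, the end of gestation period", and gives the same two time points for seroconversion and for the titre ratio. Section 7.4 defines seroconversion for women positive at baseline as "having at least a four-fold rise at 4 weeks after vaccination and at the end of gestation period". Section 7.2 admits any vaccinated woman with an evaluable post-vaccination serum, without a minimum interval. Week of gestation appears in the analysis only as a baseline descriptor (section 7.3: "including age, weight, height, gravidity and week of gestation will be reported"). Section 2.1 says that the cord titre will be compared with the maternal one, without saying which maternal sample or how close in time.

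**The concern.** The label 'end of gestation' fixes the obstetric moment but not the time since the dose, and it is the latter that governs an antibody titre. A woman vaccinated in the last days of pregnancy may give a delivery sample before she has had time to respond. A woman vaccinated at 3 months gives hers about half a year later. Both count equally in the same rate.

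A low end-of-gestation rate could then mean early sampling, waning, or a poor response, and the planned summary cannot separate these. A different mix of gestational ages at enrolment would give a different rate from the same vaccine.

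The cord–maternal comparison has a further weakness. Cord blood is fixed at birth, while the mother may be sampled weeks later, so part of any difference may come from the gap between the two samples rather than from transfer.

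**Working it through.** The protocol gives no figure for the interval from vaccination to the delivery sample, so there is none to reproduce. The range follows from its rules.

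**Inputs from the protocol**
- Minimum gestation at entry: 3 months (3.3.1). Maximum: none (3.3.1, 3.3.2).
- Visit 2 window: 3 to 5 weeks (5.1, 5.4).
- Maternal delivery sample: up to 8 weeks after delivery (5.4, 5.5).
- Sample size: 60 (3.2, 7.1).

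**Assumptions**
- 3 months = 13 weeks (range 12 to 14).
- Delivery at 40 weeks (range 37 to 42).

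**Step 1: range of intervals.** Longest interval to delivery = term − gestation at entry.

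| Case | Dose to delivery (cord) | Dose to latest maternal sample (+8) |
|---|---|---|
| Entry 13, term 40 | 40 − 13 = 27 weeks | 27 + 8 = 35 weeks |
| Shortest maximum: entry 14, term 37 | 37 − 14 = 23 weeks | 23 + 8 = 31 weeks |
| Longest maximum: entry 12, term 42 | 42 − 12 = 30 weeks | 30 + 8 = 38 weeks |

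The lower end is about 0 weeks, since a woman at term is eligible.

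**Step 2: how many deliver before a response can be expected.** The shortest post-vaccination interval that the plan accepts for Visit 2 is 3 weeks. Section 1 also reports the earlier adult seroprotection results at 3 weeks. If entry were spread evenly over 13 to 40 weeks, the share delivering within w weeks = w / (40 − 13):
- 3 weeks: 3/27 = 11.1%, or 6.7 of 60 (about 7).

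Uniform entry is an illustration only; nothing in the protocol supports it. With mid-pregnancy enrolment the share is near 0. For cord blood it is the share of samples drawn before 3 weeks. For maternal blood it is an upper limit, because the 8-week window lets an early deliverer be sampled later.

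**Step 3: what that could do to a rate.** As an extreme illustration, suppose that all of those 11.1% are sampled at delivery, that none has seroconverted, and that everyone else keeps the planning rates in section 7.1. The rate is then multiplied by 24/27:
- A/H1N1: 84.6% × 24/27 = 75.2%
- A/H3N2: 80.8% × 24/27 = 71.8%
- B: 38.5% × 24/27 = 34.2%

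This shows the early end only. Waning at the late end cannot be sized, since the protocol gives no rate of decline.

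**Step 4: the cord–maternal pair.** Take delivery 1 week after vaccination. Cord blood is drawn at week 1, and the mother may be sampled as late as week 1 + 8 = 9. The pair then compares two different points of the response.

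**The case against.** The best case for the plan has several parts.

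- **It is a matter for the SAP.** Stratified summaries and sensitivity analyses are commonly left to the SAP, which is not at hand and may contain them. This lowers the weight of the point. But the protocol itself defines the end-of-gestation rates, the population that enters them and the 8-week window, and followed as written these give a mixed result.
- **The stated outcome is status at the end of gestation.** In a single-arm descriptive study, a broad range of gestational ages is a defensible target population. This stands: the overall rate is a valid description of the women enrolled. A reader might infer that it is wrong, or that it measures nothing but the enrolment mix. The documents do not support that. The rate is confounded with the interval, not void.
- **No pooled cord rate exists.** A reader might infer one, but section 7.4 does not mention cord blood. The only cord analysis is the comparison in section 2.1. If both samples are taken at delivery they share the same interval, which removes part of the problem. The 8-week window brings it back.
- **Day 28 is anchored to vaccination.** A reader might infer bias there because some women will have delivered before Visit 2. But the sample still falls 3 to 5 weeks after a dose given in pregnancy, and nothing in the protocol shows that a postpartum draw distorts it.
- **The share may be small.** Cut-offs of 4 or 5 weeks would give 4/27 = 14.8% or 5/27 = 18.5% under uniform entry. These overstate the case, because the plan's own minimum is 3 weeks. Adherence to visits and a schedule that places Visit 2 before delivery also make term enrolment less likely than uniform entry implies.

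**Conclusion.** The point holds for the maternal end-of-gestation seroprotection rate, seroconversion rate and titre ratio, and for the cord–maternal comparison. As planned, these are confounded with time from vaccination to sampling. That time can run from about 0 to about 27 weeks for a sample taken at delivery, and to about 35 weeks for a maternal sample taken at the end of the 8-week window (13 weeks at entry, term at 40).

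The number of women affected at the early end cannot be known from the protocol: near 0 with mid-pregnancy enrolment, about 7 of 60 if entry were uniform. The Day 28 results are largely unaffected. This is a limit on interpretation that is cheap to remove, and it should be removed before the data are analysed.

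**What to change.** No change to eligibility, vaccination or visits is proposed. In section 7.4 (or the SAP):

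1. Keep the overall end-of-gestation rates and titre ratios.
2. Add maternal end-of-gestation and cord titres by weeks from vaccination to that sample's own collection date, or regress log titre on that interval.
3. Repeat the end-of-gestation rates without samples collected less than 3 weeks after vaccination, the plan's own minimum for Visit 2, and list those samples separately. Select on the sample date, not the delivery date; otherwise valid maternal samples drawn later in the 8-week window would be lost.
4. For the cord–maternal comparison, use pairs whose maternal sample was taken at or near delivery, with the limit set in advance, or adjust for the gap between the two samples.

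**Cost:** a little extra analysis, and slightly fewer women in the restricted analyses. The vaccination date goes into the case report form (4.2), and gestational week at entry and the date or week of delivery are recorded (5.1). Collection dates are needed in any case to apply the Visit 2 and 8-week windows; confirm that the case report form holds them for the delivery and cord samples.

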### **3.3.2. Exclusion criteria:**

1. Subject with previous complicated pregnancy or preterm delivery, spontaneous or medical abortion;
2. Subject with history or concurrent high risk of dangerous gestation such as gestational diabetes mellitus (GDM), pregnant induced hypertension, or preeclampsia;
3. Subject received any influenza vaccine within the previous 6 months;
4. Subject has a history of hypersensitivity to eggs or egg protein or similar pharmacological effects to study vaccine;
5. Subject or her family has the history of Guillain-Barré Syndrome;
6. Subject has current upper respiratory illness (URI), including the common cold or nasal congestion within 72 hours;
7. Subject with influenza-like illness as defined by the presence of fever (temperature  $\geq 38^{\circ}\text{C}$ ) and at least two of the following four symptoms: headache, muscle/joint aches and pains (e.g. myalgia/arthralgia), sore throat and cough;
8. Subject receive any treatment with an investigational drug or device, or participation in a clinical study, within 3 months before consent;
9. Subject has immunodeficiency or is under immunosuppressive treatment.
10. Subject received any vaccine within 1 week prior to study vaccination or expected to receive one within 1 week after study vaccination;
11. Subject received any blood products, including immunoglobulin, in the past 3 months before consent;
12. Subject has underlying condition in the investigators' opinion may interfere with evaluation of the vaccine.

## **3.4 Discontinuation for Individual Subjects**

A discontinuation is a subject who enrolled in the study and did not received the study vaccine for any reason.

The subject is free to withdraw from the study for any reason and at any time without giving reason for doing so and without penalty or prejudice. The investigator is also free to terminate

a subject's involvement in the study at any time if the subject did not received the study vaccine.

Discontinuation reason for enrolled subjects may be, but not limited to, the following:

1. Withdrawal of consent
2. Did not received study vaccine
3. Lost to follow up

The study subjects withdrawing for any reason should have a post-vaccination visit including at least all safety assessments.

There will be no replacement of withdrawn subjects, regardless of the reason for withdrawal. All subjects who experience adverse event which is ongoing either at the time of withdrawal or at the completion of whole study visit, must be followed-up at appropriate time intervals until the adverse event is resolved or judged to be no longer clinically significant, or until they become chronic to the extent that they can be fully characterized.

## **4. STUDY TREATMENT**

### **4.1 Details of Study Treatments**

The vaccine used in this study is the inactivated split influenza vaccine, licensed in Taiwan under the name AdimFlu-S. It is a sterile suspension prepared from influenza viruses propagated in chicken embryos. After the incubation, the virus-containing allantoic fluid is collected and the sucrose density gradient centrifugation is performed to isolate and concentrate the virus particles. Ether is added to lyse the virus particles and the resulting hemagglutinin (HA) fraction is recovered, inactivated by formalin, and diluted with phosphate buffered solution to formulate a final solution containing the required amount of HA of the virus strain.

Each year's influenza vaccine contains three virus strains (two type A and one type B) representing the influenza viruses that are likely to circulate in Taiwan in the coming winter. The antigenic characteristics of current and emerging influenza virus strains provide the basis for selecting the strains included in each year's vaccine.

For the 2011-2012 season, the vaccine contains not less than 90 µg hemagglutinin (HA) per

mL. The vaccine is formulated by the following three strains: [13]

|                            |          |
|----------------------------|----------|
| A/California/7/2009 (H1N1) | 30 µg/mL |
| A/Perth/16/2009 (H3N2)     | 30 µg/mL |
| B/Brisbane/60/2008         | 30 µg/mL |

The vaccine contains thimerosal  $\leq 0.005$  mg/mL as a preservative, formalin  $\leq 0.1\mu\text{L/mL}$  and polysorbate 80  $\leq 0.1\mu\text{L/mL}$  as a stabilizer.

After shaking syringe well, AdimFlu-S is essentially clear and opalescent whitish color.

The influenza virus for AdimFlu-S, Inactivated Influenza Vaccine Trivalent Types A and B (Split), is propagated in eggs, and therefore, this vaccine should not be administered to anyone with a history of hypersensitivity (allergy) and especially anaphylactic reactions to eggs or egg products. It is also a contraindication to administer this vaccine to individuals known to be sensitive to thimerosal.

## **4.2 Administration and Dosage**

Before administration of any vaccine, all appropriate precautions should be taken to prevent adverse reactions. This includes a review of the subject's history with respect to possible hypersensitivity to the vaccine or similar vaccine, determination of previous immunization history, and the presence of any contraindications to immunization, current health status, and a current knowledge of the literature concerning the use of the vaccine consideration.

In this single-dose study, the administration of the investigational product will be supervised by the investigator or sub-investigator. Each subject will receive 1 dose of vaccine (0.5 mL) by intramuscular injection into the upper arm. The injection will be given into the opposite arm from which blood was drawn.

Detail of the date of administration of study vaccine will be documented in the case report form.

## **4.3 Storage and Labeling**

Labeling for syringe will meet all official regulations. All syringes will be supplied to the clinical study site in boxes that need to be stored between 2 and 8°C and do not freeze. The study vaccine will be stored under secure conditions. Product that has been exposed to

freezing should not be used.

#### **4.4 Concomitant Vaccinations and Medications**

No concomitant immunizations (for 7 days post-vaccination) are permitted. All concomitant medications taken during the first and second venous blood samples (4 weeks post-vaccination) collected should be recorded on the case report form. Nevertheless, immunization and immunotherapies for maternal subjects after vaccination and until the end of gestation period should be recorded.

### **5. STUDY PROCEDURES AND SCHEDULE**

#### **5.1 Study Procedure**

Each potential female subject will be screened before the start of the study to determine their eligibility for participation. The following examination will be performed and documented for each subject:

- Demographics including age, height, weight, weeks of gestation and influenza vaccination at 2010-2011 season;
- Blood pressure and heart rate and ear temperature;
- Review and record all medical history including history of allergy to food, medication or blood transfusion; concurrent and prior medical conditions; and immune system disorder and smoking history.
- Review and record all obstetric history, including but not limited to the first gestational age at birth, the gravidity (the number of times a woman has been pregnant), history of previous complicated pregnancy or preterm delivery, spontaneous or medical abortion, and congenital anomaly.
- Review and record all medication taken in the past month;

Just prior to vaccination, a 10 mL venous blood sample will be taken from each eligible subject, for baseline titration of circulating anti-HA antibodies. Immediately thereafter, each subject will receive one dose of vaccine (0.5 mL) by intramuscular injection into the upper arm. The injection should be given into the opposite arm which blood was drawn. Subjects will be asked to stay at the site for 30 minutes after the vaccination to observe for immediate

reaction.

Subjects will be monitored for all adverse events during the first 4 weeks. Each subject will be instructed to record symptoms once each day (evening) on a diary card for 7 days. The following symptoms will be recorded: fever ( $\geq 38^{\circ}\text{C}$ ), nasal congestion, cough, sore throat, muscle aches, headache, nausea, vomiting, malaise, eye redness, chest tightness, respiratory distress, and face edema. Moreover the local solicited adverse events, i.e., pain, swelling, redness, ecchymosis, and decrease limb mobility, at injection site will be recorded.

At 4 weeks after vaccination, subjects will be asked to return to the site for the second collection of blood samples. All adverse events during the first 4 weeks after the vaccination should be reported and recorded. The subject may return to the site according to her regular check-up schedule but the interval between the first and second blood sampling should be at least 3 weeks apart and no more than 5 weeks.

At the end of gestation period, blood samples from maternal subjects and from the cord blood will be collected, if applicable. Pregnancy outcome, including but not limited to the status of delivery, abortion and the date and/or the week of pregnancy of the event, will be recorded. The child information, including but not limited to the birth height and weight of the infant, sex of infant, Apgar score at 1 min and 5 min, and other information specified in the CRF, will be collected. All serious adverse events and adverse events of special interest will be followed until 8 weeks after the delivery.

